### Sensitivity analyses

The following sensitivity analyses will be performed:

- Excluding participants with asthma diagnosed <5 and no current asthma (subgroup of primary outcome).
- Excluding participants with respiratory outcomes derived from hospital admission data where the respiratory diagnosis was not the primary reason for admission (subgroup of composite outcome).

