## 8. Power calculation

This study involves the follow-up of a clinical trial, and the sample size is limited to the number of participants randomised in New Zealand and able to be located. For the primary outcome of any asthma diagnosis, the sample size of 214 allows for detection of a 22% increase in the proportion with the outcome (relative risk 1.63) with 90% power ( $\beta = 0.10$ ) at a significance level of 5% ( $\alpha = 0.05$ ), assuming a baseline prevalence of 35% in the placebo group (as was found in the 6-8 year follow-up for the whole cohort).

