### Analysis approach

Analyses will be performed using an intention-to-treat approach with participants analysed according to the initial treatment group to which their mother was allocated. The denominator for the outcome of death (any cause after randomisation) will be the total number of fetuses alive at randomisation in the NZ cohort (n=352). All other study outcomes will use the total number of participants who gave consent (n=214).

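### As worded, both sensitivity analyses remove participants according to how they met the outcome; they should be counted as non-cases and kept in the denominator

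*SAP*

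**What the plan says.** The Sensitivity analyses part of SAP Section 13 (Exploratory analyses) has two bullets.

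- For the primary outcome: "Excluding participants with asthma diagnosed <5 and no current asthma (subgroup of primary outcome").
- For the respiratory composite: "Excluding participants with respiratory outcomes derived from hospital admission data where the respiratory diagnosis was not the primary reason for admission", followed by a bracket calling this a subgroup of the composite outcome.

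Neither bullet says whether the excluded people stay in the analysis as non-cases.

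Section 10 (Analysis approach) sets the general rule: "Analyses will be performed using an intention-to-treat approach with participants analysed according to the initial treatment group" to which the mother was allocated. On denominators other than that for death it says: "All other study outcomes will use the total number of participants who gave consent (n=214"). Section 13 does not say how the exclusions fit with that rule.

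Appendix 15.2 gives two routes into the respiratory composite: self-report of a respiratory condition, or a hospital admission with a listed code at any age.

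**The concern.** Both bullets ask a sensible question: does the result hold under a stricter case definition? Someone whose early asthma has gone, or whose only respiratory code was incidental to an admission, is not missing under that definition. Their status is known, and it is no event.

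Removing them takes people out of the denominator because of something observed after randomisation. If treatment changes the frequency of early transient asthma or of incidental respiratory codes, the arms lose different shares, and the groups compared are no longer those formed by randomisation. An effect confined to early transient disease could then partly reappear in the analysis meant to set it aside.

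Unequal loss is plausible but not established. SAP Section 3 reports less respiratory distress syndrome and less severe lung disease with repeat corticosteroids, and the composite counts perinatal chronic lung disease codes such as bronchopulmonary dysplasia. The same section reports no significant difference in respiratory morbidity at 2 years.

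**Working it through.** **Inputs from the SAP**

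- Section 8: "the sample size of 214", "assuming a baseline prevalence of 35% in the placebo group", "detection of a 22% increase in the proportion with the outcome (relative risk 1.63") with 90% power "at a significance level of 5"%.
- Section 10: denominator 214 for every outcome except death.

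**Assumed, because the SAP does not state it:** 107 per arm, a two-sided test, and the shares dropped. Clustering is ignored.

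**Step 1. Reproduce the SAP's figure.** Take 22% as percentage points, so 35% v 57%, and 0.57/0.35 = 1.63. The mean proportion is 0.46.

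- Standard error under the null: √(2 × 0.46 × 0.54/107) = 0.0681
- Standard error under the alternative: √((0.35 × 0.65 + 0.57 × 0.43)/107) = 0.0665
- Power: Φ((0.22 − 1.96 × 0.0681)/0.0665) = Φ(1.30) = 90.3%, against 90% stated

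The total needed for 90% power is 212, against 214 stated. The 107 per arm is therefore a fair base for illustration.

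**Step 2. Compare recoding with removal.** In each arm let p be the share who are cases under the stricter definition and e the share dropped (subscript 0 placebo, 1 repeat).

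- Recoded: RR = p1/p0, on 107 per arm
- Removed: RR = [p1/(1−e1)]/[p0/(1−e0)] = (p1/p0) × (1−e0)/(1−e1), on 107(1−e) per arm

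The extra factor is 1 only when e0 = e1.

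**Step 3. Put numbers in.** In each row p0 + e0 = 35%, matching Section 8, and the true RR for the stricter outcome is 1.00. Rejection is by the two-sided pooled z-test; with recoding it is 5% throughout.

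| p0 / p1 | e0 / e1 | n after removal (placebo / repeat) | RR after removal | Rejection |
|---|---|---|---|---|
| 25% / 25% | 10% / 10% | 96 / 96 | 1.00 | 5% |
| 25% / 25% | 10% / 20% | 96 / 86 | 0.90/0.80 = 1.13 | 8% |
| 20% / 20% | 15% / 5% | 91 / 102 | 0.85/0.95 = 0.89 | 7% |
| 25% / 25% | 10% / 32% | 96 / 73 | 0.90/0.68 = 1.32 | 24% |

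The last row is an extreme: it puts the whole of the SAP's design difference (25% + 32% = 57% in the repeat arm) into resolved early asthma.

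In whole numbers, with 21 persistent cases in each arm and 20 (placebo) v 32 (repeat) people removed, the comparison is 21/87 v 21/75, so RR = 0.280/0.241 = 1.16. Its unadjusted 95% interval is about 0.69 to 1.95, so a shift of that size is well within sampling error.

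Turning a real effect into none takes a large imbalance: a true RR of 1.40 (25% v 35%) becomes 1.40 × 0.70/0.98 = 1.00 only when 30% v 2% are dropped.

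**Step 4. The second bullet, by type of participant**

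| How the composite is met | Literal removal | Stricter definition |
|---|---|---|
| Only by a non-primary admission diagnosis | removed | non-case |
| Non-primary diagnosis and self-report | could be removed | case |
| Non-primary diagnosis and another admission with a primary respiratory diagnosis | could be removed | case |
| Primary respiratory admission only | case | case |

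Rows two and three are true cases that the wording allows to be lost.

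**The case against.** The strongest reply is that recoding was intended. A bracket that speaks of a subgroup of an outcome naturally describes which cases still count. Section 10 fixes 214 for all outcomes but death, and the enriched sample analysis, in the same Section 13, says outright that its denominators change, whereas these bullets do not. That stands as a reason to treat the text as unclear. A reader might infer that participants will certainly be dropped; the SAP does not settle this. The brackets are still only a hint, and the words that state the operation are about excluding participants. Two programmers could reasonably produce different denominators.

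A reader might also infer that these are the only robustness checks on asthma and the respiratory composite. They are not. The SAP plans adjusted and unadjusted results and an enriched sample analysis. It has a treated-asthma secondary outcome on the full denominator, though an asthma admission at any age still qualifies for it. The outcomes list in Appendix 15.2 also gives the respiratory components separately.

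The reply on size is largely right too. No dropped share is in the documents, equal shares cost only sample size, and a 10-point imbalance moves the relative risk modestly.

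**Conclusion.** The point holds on the wording, with limited reach. Literal removal conditions on a post-randomisation outcome, departs from the denominator of 214, and scales the relative risk by (1−e0)/(1−e1). There is no bias with equal shares, and a true 1.00 moves to roughly 0.9 or 1.13 with a 10-point difference. Larger distortion needs a large imbalance. All of this rests on assumed dropped shares and 107 per arm. The possible loss of true cases under the second bullet does not depend on those assumptions.

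A reader might infer that the trial's main comparison is biased or is no longer by intention to treat. The SAP does not support that: the analyses are exploratory, and the primary estimate, its denominator and its allocation rule are untouched. Nor do the documents show that an effect would in fact be created or hidden. The change is still worth making, because it removes an avoidable bias at almost no cost.

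**What to change.** Replace the two bullets with wording to this effect:

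- *Participants with asthma diagnosed before 5 years and no current asthma will be counted as not having the outcome and kept in the denominator.*
- *Participants who meet the respiratory composite only through admissions in which the respiratory diagnosis was not the primary reason will be counted as not having the outcome and kept in the denominator. Those who also qualify by self-report, or by another admission with a primary respiratory diagnosis, remain cases.*

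Report the denominators by arm for both analyses.

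The cost is two reworded bullets and a recode of existing variables, with no new data. The SAP has already been amended by addendum, so the route exists. If treatment groups have been unblinded, present the recoded version and label it as a later change, in line with the SAP's own rule on post hoc analyses.

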### Post hoc analyses

Any post-hoc, exploratory analyses which were not identified in this SAP but are completed to support the listed analyses will be identified clearly.

## 15. Appendix

### 15.1. Flow diagram

[figure not shown]

## 15.2. Outcomes list

### Primary Outcome

- Any asthma diagnosis

### Secondary Outcomes:

- Asthma currently on treatment
- Death (any cause after randomisation)
- Respiratory outcomes (composite) – any respiratory diagnoses other than asthma including chronic lung disease
- Neurodevelopmental disability (composite) – any of:
  - visual impairment
  - hearing impairment
  - intellectual impairment
  - cerebral palsy
  - epilepsy
  - autism spectrum disorder (including Asperger's syndrome)
  - attention deficit disorder (ADD) or attention deficit hyperactivity disorder (ADHD)
- Cardiovascular outcomes (composite) – any cardiovascular diagnosis including hypertension, cardiomyopathies, arrhythmias, heart failure
- Number of cardiovascular disease risk factors (composite categorised as 0, 1 or >1 risk factors) – any of:
  - high blood pressure
  - dyslipidaemia
  - diabetes mellitus
  - obesity/overweight
- Diabetes outcomes (composite) – any of prediabetes, diabetes mellitus, gestational diabetes mellitus
- Mental health outcomes (composite) – any mental health diagnosis including depression, bipolar affective disorder, schizophrenia, anxiety disorders, suicide/self-harm
- Bone health outcomes: any diagnoses related to bone disease
- Bone health outcomes: number of fractures
- General health outcomes: self-reported general health (reported health fair or poor)
- General health outcomes: functional difficulties (categorised as no disability / moderate or non-severe disabilities / severe disabilities)
- General health outcomes: oral health (reported oral health fair or poor or tooth extractions)

### Tertiary Outcomes:

- Educational achievement outcomes: no secondary school qualification
- Educational achievement outcomes: any disciplinary action
- Social outcomes: any convictions
- Social outcomes: unemployment
- Social outcomes: alcohol use in the past year
- Social outcomes: recreational drug use
- Social outcomes: past/current smoking (pack years)
- Social outcomes: past/current vaping
- Components of respiratory composite outcome:
  - Respiratory infections
  - Chronic respiratory conditions (excluding asthma)
  - Respiratory failure
  - Respiratory trauma
- Components of neurodevelopmental disability composite outcome:
  - visual impairment
  - hearing impairment
  - intellectual impairment
  - cerebral palsy
  - epilepsy
  - autism spectrum disorder (including Asperger's syndrome)

- attention deficit disorder (ADD) or attention deficit hyperactivity disorder (ADHD)
- Components of cardiovascular composite outcome:
  - Hypertension
  - Cardiomyopathies
  - Arrhythmias
  - heart failure
- Components of cardiovascular disease risk factors composite outcome:
  - high blood pressure
  - dyslipidaemia
  - diabetes mellitus
  - obesity/overweight
- Components of diabetes composite outcome:
  - prediabetes/diabetes mellitus
  - gestational diabetes mellitus
- Components of mental health composite outcome
  - depression
  - bipolar affective disorder
  - anxiety disorders
  - suicide/self-harm
  - schizophrenia
- Components of functional difficulties outcome
  - Difficulty seeing, even if wearing glasses
  - Difficulty hearing, even if using a hearing aid
  - Difficulty walking or climbing steps
  - Difficulty remembering or concentrating
  - Difficulty washing all over or dressing
  - Difficulty communicating
- Components of obesity/overweight outcome
  - BMI
  - height
  - weight

| Study Outcome (definitions)                                                                                                                                                                                                                                                                                                                                          | Priority Order for use of Data Sources | Details of data*:                                                                                                                                                                                                                                                                                                                                                                                           | Criteria for adjudication (if applicable)                                                                          | Comments/ Reference:                                                                                                                                                                                                |
|----------------------------------------------------------------------------------------------------------------------------------------------------------------------------------------------------------------------------------------------------------------------------------------------------------------------------------------------------------------------|----------------------------------------|-------------------------------------------------------------------------------------------------------------------------------------------------------------------------------------------------------------------------------------------------------------------------------------------------------------------------------------------------------------------------------------------------------------|--------------------------------------------------------------------------------------------------------------------|---------------------------------------------------------------------------------------------------------------------------------------------------------------------------------------------------------------------|
| Primary outcome                                                                                                                                                                                                                                                                                                                                                      |                                        |                                                                                                                                                                                                                                                                                                                                                                                                             |                                                                                                                    |                                                                                                                                                                                                                     |
| Any asthma diagnosis
Defined as the presence of either of: 
 
Self-report of a doctor's diagnosis of asthma.
 
Hospital admissions with diagnostic codes for asthma at any age.
 
Dispensing of pharmaceuticals for asthma at any age at least one repeat prescription more than 1 day apart.
 
 | Self-report questionnaire              | B22. Have you ever been told by a doctor that you have asthma?                                                                                                                                                                                                                                                                                                                                              | If answers no to question about asthma but has evidence from only one other data source, then will be adjudicated. |                                                                                                                                                                                                                     |
|                                                                                                                                                                                                                                                                                                                                                                      | NMDS admissions data                   | Admissions with the following ICD-10AM codes:
J45.0 – J45.998 Asthma and subcodes.
J46 status asthmaticus
R06.2 Wheezing
U833 Asthma, without mention of chronic obstructive pulmonary disease                                                                                                                                                                                                  |                                                                                                                    | https://www.hqsc.govt.nz/assets/Our-data/Publications-resources/Methodology-asthma-update-2020.pdf |
|                                                                                                                                                                                                                                                                                                                                                                      | NZ pharmaceuticals collection          | Prescriptions + dates
Short acting beta agonist (SABA):
Salbutamol ( Ventolin, respigen, SalAir ), terbutaline ( Bricanyl ).
Long acting beta agonists (LABA):
Eformoterol fumarate ( Oxis, Foradil ), salmeterol ( Serevent, Meterol ),
Inhaled corticosteroid (ICS):
Beclometasone dipropionate ( Beclazone, Qvar ), budesonide |                                                                                                                    | https://www.hqsc.govt.nz/assets/Our-data/Publications-resources/Methodology-asthma-update-2020.pdf |

| Study Outcome (definitions)                                                                                                                                                                                                                                                                                                                                                                         | Priority Order for use of Data Sources | Details of data*:                                                                                                                                                                                                                                                                                                                                                                                                                                                                                                               | Criteria for adjudication (if applicable)                                                                    | Comments/ Reference:                                                                                                                                                                                                                                                                                                       |
|-----------------------------------------------------------------------------------------------------------------------------------------------------------------------------------------------------------------------------------------------------------------------------------------------------------------------------------------------------------------------------------------------------|----------------------------------------|---------------------------------------------------------------------------------------------------------------------------------------------------------------------------------------------------------------------------------------------------------------------------------------------------------------------------------------------------------------------------------------------------------------------------------------------------------------------------------------------------------------------------------|--------------------------------------------------------------------------------------------------------------|----------------------------------------------------------------------------------------------------------------------------------------------------------------------------------------------------------------------------------------------------------------------------------------------------------------------------|
|                                                                                                                                                                                                                                                                                                                                                                                                     |                                        | 
(Pulmicort), fluticasone propionate (Flixotide, Floair)
 
Combination of LABA and ICS:
 fluticasone + salmeterol (Seretide, RexAir), budesonide + formoterol (Symbicort, DueResp Spiromax, Vannair), fluticasone furoate + vilanterol (Breo Ellipta, Relvar Ellipta)
 
Combination of SABA and SAMA:
 Salbutamol + ipratropium bromide
 
Oral Treatments
 Montelukast (Montelukast Mylan, Apo-Montelukast, Montelukast Accord)
 |                                                                                                              |                                                                                                                                                                                                                                                                                                                            |
| Secondary outcomes                                                                                                                                                                                                                                                                                                                                                                                  |                                        |                                                                                                                                                                                                                                                                                                                                                                                                                                                                                                                                 |                                                                                                              |                                                                                                                                                                                                                                                                                                                            |
| 
Asthma currently on treatment
 
Defined as the presence of either of:
 
 
1. Self-report of a doctor's diagnosis of asthma AND currently on treatment.
 
2. Hospital admissions with diagnostic codes for asthma at any age.
 
3. Dispensing of pharmaceuticals for asthma for at least one repeat prescription more
 
 | Self-report questionnaire              | 
B22. Have you ever been told by a doctor that you have asthma?
 
B23. What treatments do you now have for asthma?
                                                                                                                                                                                                                                                                                                                                                                                                   | If answers no to question about asthma but has evidence from one other data source then will be adjudicated. | 
Timeframe of last 2 years to account for those with seasonal asthma who may only have received their last script last season.
 
Administrative data will be right censored at the date of the questionnaire for participants who completed the questionnaire and at the date of consent for those who did not.
 |

| Study Outcome (definitions)               | Priority Order for use of Data Sources | Details of data*:                                                                                                                                                                                                                                                                                                                                                                                                                                                                                                                                                                                                                                                                                                                                                                                                   | Criteria for adjudication (if applicable) | Comments/ Reference:                                                                                                                                                                                                |
|-------------------------------------------|----------------------------------------|---------------------------------------------------------------------------------------------------------------------------------------------------------------------------------------------------------------------------------------------------------------------------------------------------------------------------------------------------------------------------------------------------------------------------------------------------------------------------------------------------------------------------------------------------------------------------------------------------------------------------------------------------------------------------------------------------------------------------------------------------------------------------------------------------------------------|-------------------------------------------|---------------------------------------------------------------------------------------------------------------------------------------------------------------------------------------------------------------------|
| than 1 day apart and within last 2 years. |                                        |                                                                                                                                                                                                                                                                                                                                                                                                                                                                                                                                                                                                                                                                                                                                                                                                                     |                                           |                                                                                                                                                                                                                     |
|                                           | NMDS admissions data                   | Admissions with the following ICD-10AM codes:
J45.0 – J45.998 Asthma and subcodes.
J46 status asthmaticus
R06.2 Wheezing                                                                                                                                                                                                                                                                                                                                                                                                                                                                                                                                                                                                                                                                                   |                                           | https://www.hqsc.govt.nz/assets/Our-data/Publications-resources/Methodology-asthma-update-2020.pdf |
|                                           | NZ pharmaceuticals collection          | Prescriptions + dates
Short acting beta agonist (SABA):
Salbutamol ( Ventolin, respigen, SalAir ), terbutaline ( Bricanyl ).
Long acting beta agonists (LABA):
Eformoterol fumarate ( Oxis, Foradil ), salmeterol ( Serevent, Meterol ),
Inhaled corticosteroid (ICS):
Beclometasone dipropionate ( Beclazone, Qvar ), budesonide ( Pulmicort ), fluticasone propionate ( Flixotide, Floair )
Combination of LABA and ICS:
fluticasone + salmeterol ( Seretide, RexAir ), budesonide + formoterol ( Symbicort, DueResp Spiromax, Vannair ), fluticasone furoate + vilanterol ( Breo Ellipta, Relvar Ellipta )
Combination of SABA and SAMA:
Salbutamol + ipratropium bromide |                                           | https://www.hqsc.govt.nz/assets/Our-data/Publications-resources/Methodology-asthma-update-2020.pdf |

| Study Outcome (definitions)                                                                                                                                                                                                                                           | Priority Order for use of Data Sources | Details of data*:                                                                                                                                                                                                                              | Criteria for adjudication (if applicable) | Comments/ Reference: |
|-----------------------------------------------------------------------------------------------------------------------------------------------------------------------------------------------------------------------------------------------------------------------|----------------------------------------|------------------------------------------------------------------------------------------------------------------------------------------------------------------------------------------------------------------------------------------------|-------------------------------------------|----------------------|
|                                                                                                                                                                                                                                                                       |                                        | Oral Treatments
Montelukast ( Montelukast Mylan, Apo-Montelukast, Montelukast Accord )                                                                                                                                        |                                           |                      |
| Death (any cause after randomisation)                                                                                                                                                                                                                          | MORT data                              | Death from any cause obtained from MORT dataset                                                                                                                                                                                                |                                           |                      |
|                                                                                                                                                                                                                                                                       | Trial follow up records                | Death from any cause as recorded in databases for original trial data and earlier follow-up studies.                                                                                                                                           |                                           |                      |
| Respiratory outcomes (composite)
Defined as the presence of either of: 
 
Self-report of a respiratory condition.
 
Hospital admissions with diagnostic codes for a respiratory condition at any age.
 
 | Self-report questionnaire              | Free text response indicating a respiratory condition to one of the following questions:
B41. Do you currently have any other major illnesses?
B42. Have you ever had any other major illnesses in the past?                             |                                           |                      |
|                                                                                                                                                                                                                                                                       | NMDS admissions data                   | Admissions with the following ICD-10AM codes:
J121 Respiratory syncytial virus pneumonia
J129 Viral pneumonia, unspecified
J13 Pneumonia due to Streptococcus pneumoniae
J150 Pneumonia due to Klebsiella pneumoniae |                                           |                      |

| Study Outcome (definitions) | Priority Order for use of Data Sources | Details of data*:                                                                                                                                                                                                                                                                                                                                                                                                                                                                                                                                                                                                                                                                                                                                                                             | Criteria for adjudication (if applicable) | Comments/ Reference: |
|-----------------------------|----------------------------------------|-----------------------------------------------------------------------------------------------------------------------------------------------------------------------------------------------------------------------------------------------------------------------------------------------------------------------------------------------------------------------------------------------------------------------------------------------------------------------------------------------------------------------------------------------------------------------------------------------------------------------------------------------------------------------------------------------------------------------------------------------------------------------------------------------|-------------------------------------------|----------------------|
